|                      |                                                                                                                                                                                                                                                                                                                                                                                                               |
|----------------------|---------------------------------------------------------------------------------------------------------------------------------------------------------------------------------------------------------------------------------------------------------------------------------------------------------------------------------------------------------------------------------------------------------------|
|                      | Single-center study (only 1 center involved in patient inclusion)                                                                                                                                                                                                                                                                                                                                             |
| Statistical analysis | No intermediate analysis. Quantitative variables will be described by their means and standard deviation, and qualitative variables by their absolute and relative frequencies. Depending on the normality of the distribution of the quantitative variables of interest, they will be compared using a rank comparison test (Wilcoxon test) or a mean comparison test (Student's t-test for paired samples). |
| Source of financing  | HUPC Research Department (APHP) and Fonds Luc (King Baudoin Foundation)                                                                                                                                                                                                                                                                                                                                       |

## **2 SCIENTIFIC JUSTIFICATION OF RESEARCH**

### **2.1 CURRENT STATE OF RESEARCH KNOWLEDGE**

#### **2.1.1 On pathology**

Non-specific low back pain is the leading cause of years lived with disability worldwide (Disease GBD, Lancet 2017). It becomes chronic when its duration of evolution exceeds 12 weeks and then represents the leading cause of disability at work (Palazzo et al., 2016). The network of biological, psychological and social contributors to chronic low back pain is complex. Within this network, physical and psychic deconditioning to exercise is central and is a preferred therapeutic target of multidisciplinary exercise retraining programs.

Chronic low back pain is associated with physical deconditioning, defined as a reduction in spinal mobility and muscle performance.

#### **On reference strategies/procedures**

To take account of the multifactorial and complex nature of low back pain, the biopsychosocial model has been favoured in recent decades.

It has led to the emergence of standardized intensive multidisciplinary programs based on exercise retraining (ERT), combining education, exercise therapy, physical activity, occupational therapy and psychological and social rehabilitation (Rozenberg et al., 2012). Functional restoration programs aimed at combating physical deconditioning characterized by reduced spinal mobility and muscular performance of the spinal muscles, include stretching exercises for the sub-pelvic muscles and muscle strengthening (Mayer et al., 1985).

Exercise improves pain and function in chronic low-back pain (Hayden et al., 2005, Koes et al., 2006). However, its benefits diminish if it is not continued on a regular basis (Taimela et al., 2000). The enjoyment of physical exercise and the possibility of integrating it into daily life are important factors in adherence (McArthur et al., 2014). Gardening is well suited to the physical treatment of chronic low back pain, since it involves working on spinal flexibility (during activities such as weeding and leaf collection, etc.), strength and endurance of spinal and limb muscles (carrying bags of soil, carrying tools, handling watering cans, etc.) and proprioceptive adjustments (walking on more or less stable ground, digging on more or less hard ground, etc.). What's more, gardening is an activity with tangible objectives and results. Associated with the notion of pleasure, it can be practised in a group, fostering social ties. Gardening is suitable for the long term, and can even be practised in town (community gardens...).

Chronic pain is associated with affective disorders such as anxiety and depression (Landa et al., 2012). Pain sensations are in fact modulated by affective and emotional state (Sullivan et al., 2001). Within the pain neuro-matrix, the anterior cingulate cortex plays an important role in encoding pain and associated emotions (Vogt, 2005). It also acts as an interface between cognition and emotion (Dum et al., 2016). In major depressive pathologies, connections between the default brain network and the anterior cingulate cortex are strengthened and perfusion of the anterior cingulate cortex is increased (Hamilton et al., 2015). Activation of the anterior cingulate cortex is particularly linked to rumination, defined as the intrusion of involuntary and difficult-to-control thoughts (Kuehner and Weber, 1999, Nolen-Hoeksema, 2000).

Several studies suggest an impact of a "nature experience", even of short duration, on several physiological parameters: brain activity, autonomic nervous system, hormonal and immune system (Franco et al., 2017, Hansen et al., 2017). Simply seeing plants is said to induce a decrease in prefrontal cortex activity measured on MRI, stabilization of autonomic nervous activity measured by heart rate regularity and a feeling of well-being (White et al., 2013, Ikei et al., 2014, Park et al., 2016). The physiological mechanisms behind these effects remain incompletely elucidated. Several theories are proposed to support the effects of nature on health and well-being. According to attention restoration theory, a natural environment produces stimuli that enable the subject to decentralize and thus reduce attentional fatigue linked to cognitive tasks (Kaplan and Kaplan, 1999). According to stress recovery theory, an extension of the biophilic hypothesis, man is innately connected to nature. Nature is therefore a necessary building block for development, balance and adaptation to stress (Ulrich, 1983). In a randomized controlled trial published in 2015 in the journal PNAS, conducted in 38 healthy volunteers, Bratman and colleagues compared the effect of a 90-

min walk in nature (forest) with a 90-min walk in an urban environment (city) on activation of the anterior cingulate cortex, assessed by means of MRI blood perfusion variation, and on rumination, assessed by means of a self-questionnaire (Bratman et al., 2015). The authors showed that neural activation in the anterior cingulate cortex and rumination scores were lower in the group of healthy volunteers exposed to nature (Bratman et al., 2015). A cross-over study showed beneficial effects of a nature walk on mood and particularly rumination in patients with major depressive disorder (Berman et al., 2012). A randomized controlled trial showed that patients in the sub-acute phase of a stroke adhered widely to a nature-based activity program (Palsdottir et al., 2020). The impact of a "nature experience" on chronic low back pain has been little studied (Hyunju et al., 2019). A non-randomized controlled study showed the effectiveness of adding 7 horticultural therapy sessions to a standardized pain management program, on the health status, anxiety and coping strategies of chronic pain patients (fibromyalgia and chronic low back pain) (Verra et al., 2012).

Through its dual nature-experimental and physical components, horticultural therapy could be a precision non-pharmacological intervention in people with chronic low back pain, targeting both the neurobiological and physical aspects of exercise deconditioning. Horticultural therapy was introduced in October 2017 into the multidisciplinary exercise retraining programs dedicated to chronic low back pain in our department. However, its effects have not yet been evaluated.

## **2.2 Research hypotheses**

We hypothesize that horticultural therapy may reduce activation of the anterior cingulate cortex. Its effects could be mediated by dual exposure to both nature and physical activity. The pilot dimension of this study is in line with the methodological structuring of complex interventions recommended by the Medical Research Council.

## **2.3 Description of the population to be studied and justification for its choice**

Participants will be recruited from chronic low-back pain sufferers for whom rehabilitation is indicated.

## **2.4 Description of procedures performed in accordance with their current use**

Horticultural and handiwork activities have been part of the routine care of chronic low-back pain patients in our department for many years (25 years for the handiwork workshop and 3 years for the horticultural workshop). The horticultural and handiwork activities are supervised by experienced professionals (occupational therapists) (> 10 years' experience), well-versed in running therapeutic workshops.

Participants will be in groups of 4, to perform for 90 minutes 2 times a week, 2 consecutive days, on 1st or 3rd week: the horticulture activity (intervention) and 2 times a week on 1st or 3rd week, the handiwork activity (comparator). The HANDIWORK activity was chosen as comparator because the level of physical activity proposed is comparable to that of gardening (comparable approximate energy expenditure value, (Ainsworth et al., 2000) and exposure to nature is nil. The 2 activities involve handling tasks: lifting an object off the ground and carrying it, and forward-leaning standing postures reproducing the conditions of use of the spine in multiple occupational and daily activities, and soliciting the spinal muscles (deficient in chronic low-back pain patients, Demoulin et al., 2007).

[figure not shown]

### Contents of horticultural and HANDIWORK workshops :

Horticultural workshop: this workshop will be supervised by an experienced occupational therapist in collaboration with the hospital's gardeners.

The tasks performed will be :

- Handling tasks (moderate loads (maximum load: 8 kg), standing): carrying tools (rake, spade, wheelbarrow, pruning shears...), carrying bags of potting soil, handling full watering cans (approx. 20 min).
- gardening tasks (standing, leaning forward (forward lunge), crouching or kneeling, etc.): weeding, picking up plants from the ground and from raised containers, digging, cutting, planting, watering, mulching, picking fruit and vegetables from the vegetable garden (approx. 70 min.)

The content of gardening tasks depends on the season and the gardener's planning of activities. In the event that weather conditions make outdoor work difficult, horticultural activities in the greenhouse: handling, planting, cutting, making cuttings... are possible (standing and sitting up high). The greenhouse was financed by the Trophée patients AP-HP 2018, "coup de cœur du jury" prize).

Do-it-yourself workshop: this workshop will be supervised by an experienced occupational therapist.

The tasks performed will be :

- handling tasks (moderate loads (maximum load: 8 kg), in standing position): transport (wood, etc.) between the technical services and the occupational therapy room (the 2 buildings are approximately 200 m apart, duration of these tasks, approximately 20 min)
- actual handiwork tasks standing, leaning forward (forward lunge), crouching or kneeling ): taking measurements, cutting wood (1 cm thick boards) with a hand saw, assembling, finishing (approx. 70 min.)

The aim of these handiwork tasks is to build a small wooden cabinet to store occupational therapy equipment.

To consolidate the description of activities, we used the TIDieR item list.

## **2.5 Description of acts and procedures added by search**

The procedures added by the research will be brain MRIs. These will be performed at Hôpital St Anne on a Canon Galan 3T XGO clinical MRI unit. Patients will be positioned supine in the MRI ring, with their arms at their sides, and protected against noise pollution (earplugs). A 32-channel surface antenna will be installed for image acquisition.

The total duration of the exam is approximately 35 minutes. It will consist of 3 sequences:

- high-resolution T1-weighted image for anatomical reference (Canon sequence: 3D FAST FE, equivalent to MPRAGE)
- ASL, perfusion-weighted image (Canon sequence: ASTAR)
- PD, proton density-weighted image for quantitative CBF measurement (Canon sequence: ASTAR, with long TR)

No injection of contrast medium will be performed.

## **2.6 Summary of foreseeable and known benefits and risks for research subjects e**

With its dual experimental nature and physical component, horticultural therapy could be a precision non-pharmacological intervention for people with chronic low back pain, targeting both the neurobiological and physical aspects of exertional deconditioning. Therapeutic horticulture also has the advantage of being practicable over the long term.

The risks are minimal:

- related to the adverse events most frequently reported during moderate-intensity physical activity: pain, fatigue and musculoskeletal injuries.
  - related to handling handiwork and gardening tools (skin injuries)
  - if known contraindications are respected: pacemaker, cochlear and intraocular metallic implants, these risks are low. These contraindications will have been ruled out at the inclusion visit.
  - related to patients' walking distance (approx. 1km) between Hôpital Cochin and Hôpital Sainte-Anne (patients will be accompanied by a member of the rehabilitation team during these journeys).
  - for the horticultural workshop, patients will be equipped with safety shoes, gardening gloves and, depending on weather conditions, a waterproof coat. For the handiwork activity, patients will be equipped with safety shoes, protective gloves and goggles (for cutting tasks). The department already has and uses this equipment, which is cleaned/disinfected between each use.
- Thanks to the use of specially adapted equipment, and the constant supervision of the activity by caregivers who explain and demonstrate the movements to be carried out, and assist patients encountering difficulties, we have not had to deplore any injuries (apart from a few rare blisters and splinters when patients were not wearing gloves).

Given the current health situation, and in the absence of new recommendations, all patients will be equipped with disposable masks, hands will be systematically washed with SHA before starting work, and gloves will be put on. We will also ensure physical distancing between patients and between patients and staff.

### 3 OBJECTIVES DE LA RECHERCHE

#### 3.1 Main research objective

The main objective was to evaluate the efficacy of horticultural therapy in reducing activation of the anterior cingulate cortex in people with chronic low back pain subjected to 2 sessions of 90 min of horticultural therapy versus 2 sessions of 90 min of HANDIWORK.

#### 3.2 Secondary research objectives

The secondary objectives are :

- to compare the change in rumination score and dramatization score in patients with chronic low back pain after 2 sessions of 90 min of horticultural therapy versus 2 sessions of 90 min of handiwork.
- gather patient feedback on activities.

### 4 RESEARCH DESIGN

#### 4.1 Primary endpoint

The primary endpoint is the change in anterior cingulate cortex activity measured by the change in blood perfusion in ml/100 g tissue/min.

The change in blood perfusion in the anterior cingulate cortex after the first exposure (MRI #2 - MRI #1) will be compared with the change after the second exposure (MRI #3 - MRI #1).

MRI n°1 will be performed before the start of the 1st activity session of the 1st treatment sequence (1st week: 1st exposure), MRI n°2 will be performed as soon as possible and no later than 3 hours after the end of the 2nd activity session, during the last day of activity of the 1st week (1st exposure), MRI n°3 will be performed as soon as possible and no later than 3 hours after the end of the 2nd activity session of the 2nd treatment sequence, during the last day of activity of the 3rd week (3rd week: 2nd exposure). The patient's activity schedule will be adjusted to ensure that the 3-hour delay between the end of the activity and the MRI is respected for each patient.

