| Objective and primary endpoint     | The main objective is to evaluate the efficacy of horticultural therapy in reducing activation of the anterior cingulate cortex in people with chronic low back pain subjected to 2 sessions of 90 min of horticultural therapy and 2 sessions of 90 min of handiwork.

The primary endpoint is the change in blood perfusion of the anterior cingulate cortex (in ml/100 g tissue/min) after the first exposure (MRI #2 - MRI #1) compared with the change after the second exposure (MRI #3 - MRI #1). |
| Objectives and secondary endpoints | The secondary objectives are :
- to compare the variation in: rumination score and dramatization score in patients with chronic low back pain after 2 sessions of 90 min of horticultural therapy versus 2 sessions of 90 min of handiwork.
-gather patient feedback on activities.

The quantitative secondary endpoints will be :
- variation in rumination score measured by the self-administered Rumination Reflection Questionnaire (Trapnell and Campbell, 1999).                        |

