## 5 DESCRIPTION OF RESEARCH METHODOLOGY

### 5.1 Experimental design

Pilot randomized controlled cross-over study in the Department of Re-education and Rehabilitation of the Musculoskeletal System and Rachis Pathologies at Hôpital Cochin (Pr [name]) using a mixed methodology (quantitative and qualitative).

Participants will be their own controls and will be randomized in a 1:1 ratio to receive a sequence of treatments involving the experimental intervention (horticulture) in either stage 1 or stage 3, separated by a wash-out stage.

Therapists and participants will not be blinded to the treatment sequence, but the neuroradiologist and biostatistician will be.

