### 7.3 Recruitment procedures

*Justification of recruitment capacity with regard to the number of subjects to be included ;*

A difference of 7 ml/100 g tissue/min (SD=4) between perfusion changes in the anterior cingulate cortex after the 2 horticultural therapy sessions and after the 2 handiwork sessions is estimated to be clinically relevant (Bratman et al., 2015). Given this expected difference, a risk  $\alpha$  of 5%, a power of 90%, and a potential lost to follow-up of 20%, we planned to include a total of 16 patients.

Participants will be recruited from among patients seen in consultation by a doctor in the department or a doctor attached to the department. Participants will also be informed of the study by means of posters displayed in the Department of Re-education and Rehabilitation of the Musculoskeletal System and Spine Pathologies at Cochin Hospital, and in the waiting rooms of the private practices of doctors attached to the department (Appendix J and K). A patient included in the study will be able to call on his or her own network of acquaintances (recruitment based on the snowball effect). In the department it is during a consultation that the physician (-investigator) asks the patient if he or she agrees to be contacted by telephone about a study.

|                                                   | Number of subjects |
|---------------------------------------------------|---------------------------|
| Total number of subjects selected          | 16                        |
| Number of recruiting centers               | 1                         |
| Inclusion period (months)                  | 12                        |
| Number of subjects / center                | 16                        |
| Number of subjects / center / month | 1,3                |

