## 9 EVALUATION OF EFFECTIVENESS

### 9.1 Description of evaluation parameters of efficacy

The primary endpoint is the change in anterior cingulate cortex activity measured by the change in blood perfusion in ml/100 g tissue/min. The change in blood perfusion of the anterior cingulate cortex after the first exposure (MRI n°2 - MRI n°1) will be compared with the change after the second exposure (MRI n°3 - MRI n°1). MRI n°1 will be performed before the start of the 1st activity session (1st week: 1st exposure), MRI n°2 will be performed after the end of the 2nd activity session, during the last day of activity of the 1st week (1st exposure), MRI n°3 will be performed after the end of the 2nd activity session during the last day of activity of the 3rd week (3rd week: 2nd exposure).

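### The primary endpoint compares first with second exposure rather than horticulture with handiwork, so with 1:1 sequences and a paired test it measures the period effect and the treatment effect cancels

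*Protocol*

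**What the plan says.** The primary comparison is defined three times, each time by order of exposure:

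- Section 4.1: the change "after the first exposure (MRI #2 - MRI #1) will be compared with the change after the second exposure (MRI #3 - MRI #1".
- Synopsis, primary endpoint: the change "after the first exposure (MRI #2 - MRI #1) compared with the change after the second exposure (MRI #3 - MRI #1".
- Section 9.1: the change "after the first exposure (MRI n°2 - MRI n°1) will be compared with the change after the second exposure (MRI n°3 - MRI n°1".

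An exposure here is a period, not an activity. The synopsis (experimental diagram) makes the first exposure whichever activity randomisation assigns and the second exposure the other one. Section 5.1 has participants "randomized in a 1:1 ratio to receive a sequence of treatments involving the experimental intervention (horticulture) in either stage 1 or stage 3".

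Elsewhere the comparison is by activity. The main objective in section 3.1 concerns patients "subjected to 2 sessions of 90 min of horticultural therapy versus 2 sessions of 90 min of HANDIWORK". The sample size in section 7.3 rests on a difference of 7 (SD 4) "between perfusion changes in the anterior cingulate cortex after the 2 horticultural therapy sessions and after the 2 handiwork sessions". The quantitative secondary endpoints in section 4.1 are also worded as horticultural therapy against handiwork.

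Section 13 names a paired t-test or a Wilcoxon test, depending on normality, without saying what forms the pair. On blinding, section 5.1 says: "Therapists and participants will not be blinded to the treatment sequence, but the neuroradiologist and biostatistician will be".

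**The concern.** In a two-period crossover, first minus second exposure is the treatment effect plus the period difference in one sequence, and the period difference minus the treatment effect in the other. If these are pooled over a 1:1 randomisation and tested against zero, the treatment effect averages out and the period difference remains.

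The error can mislead in both directions. A real horticulture effect would be missed. A drift in perfusion between week 1 and week 3 that has nothing to do with horticulture (scanner, season, habituation to the examination) would be read as a positive primary result.

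**Working it through.** **Inputs.** Effect 7 and SD 4 ml/100 g/min, alpha 5%, power 90%, 20% lost to follow-up, N = 16 (synopsis and section 7.3). Allocation 1:1 (section 5.1). Paired t-test (section 13).

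**Assumptions.** The test is two-sided. SD 4 is the SD of the within-patient difference; the protocol does not settle this, so 4√2 = 5.66 (SD 4 per change, zero correlation) is shown as well. The horticulture effect is a reduction, so −7. Period shifts and unequal splits are illustrations. With 20% loss, 16 × 0.8 = 12.8, about 13 completers.

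**Plan's own figure.** The stated 16 is close to what a two-group formula gives: 2 × (1.960 + 1.282)² × 4² / 7² = 6.9, so 7 per group and 14 in total, or 18 after dividing by 0.8 (17 if multiplied by 1.2). With the exact t distribution, 8 per group gives 90.2% power before any loss. Whatever formula was used, the difference of 7 is horticulture against handiwork.

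**Algebra.** The baseline cancels:

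(MRI #2 − MRI #1) − (MRI #3 − MRI #1) = MRI #2 − MRI #3.

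Let τ be horticulture minus handiwork, π the period difference (first minus second), and nA and nB the completers in the horticulture-first and handiwork-first sequences.

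- Horticulture first: expected value π + τ.
- Handiwork first: expected value π − τ.
- Pooled: π + τ(nA − nB)/(nA + nB), which is π when nA = nB.

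**A true effect, no period effect (τ = −7, π = 0), contrast as worded:**

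| Split nA:nB | Expected contrast | Rejection, SD 4 | Rejection, SD 5.66 |
|---|---|---|---|
| 8:8 | 0 | 0.01% | 0.2% |
| 7:6 | −7 × 1/13 = −0.54 | 0.03% | 0.3% |
| 9:7 | −7 × 2/16 = −0.88 | 0.1% | 0.6% |
| 8:5 | −7 × 3/13 = −1.62 | 0.6% | 1.7% |
| 10:6 | −7 × 4/16 = −1.75 | 1.3% | 2.9% |

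Rejection falls below the nominal 5% because the opposite-signed effects widen the spread of the pooled differences to about √(4² + 7²) = 8.1 while their mean stays near zero. Re-indexed as horticulture minus handiwork, the expected value is −7 and rejection is at least 99.9% for every split at SD 4. At SD 5.66 it is 99.6% with 16 patients and 98.3% with 13.

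**No treatment effect, a period shift only (τ = 0), contrast as worded:**

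| Assumed shift | 16 patients, SD 4 | 13 patients, SD 4 | 16 patients, SD 5.66 | 13 patients, SD 5.66 |
|---|---|---|---|---|
| 1 | 16% | 13% | 10% | 9% |
| 2 | 47% | 38% | 26% | 22% |
| 3 | 80% | 70% | 51% | 42% |
| 4 | 96% | 91% | 75% | 65% |

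With a shift of 4, 8:8 sequences and SD 4, the paired test by activity rejects in 0.6% of trials and the period-adjusted crossover test in 5%.

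**The case against.** **The intent is clear.** The objective, the secondary endpoints and the sample-size text all point to horticulture against handiwork, and the order wording may have been drafted around a single example sequence, as in section 6. This stands as a limit: the text does not prove that the final analysis will be run by order. It does not rescue the definition, because the sentence that fixes the primary comparison is wrong in all three places and no correct version appears.

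**The statistical analysis plan may correct it.** That plan is not at hand. But the protocol does not leave the contrast open. A plan that followed it would inherit the error, and one that departed from it would contradict the protocol's primary endpoint.

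**MRI #2 − MRI #3 is not useless.** Compared between the two sequences, it gives the standard crossover estimate of treatment. This is correct. The failure comes from the order definition combined with the paired test in section 13, which pools over sequences.

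**Blinding.** The protocol says only that the biostatistician is blinded to sequence. It does not say that a masked code is withheld, so this is not a separate error. It does add risk: without some sequence code, the by-order contrast is the only one that can be computed.

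**The size of the false-positive risk depends on assumptions.** This is fair. No period shift is given in the documents, and section 5.3.2 chose the three-week span to limit natural evolution of symptoms. The cancellation at equal sequences needs no such assumption.

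**Conclusion.** The concern holds. As written, and with the paired test of section 13, the primary comparison estimates the period difference plus τ(nA − nB)/n, and it conflicts with the protocol's own objective and sample-size basis. Cancellation is exact with equal completers per sequence; at 10:6 only 1.75 of the 7 remains.

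With no period effect, rejection under a true effect of 7 is at most about 1.3% over the splits examined at SD 4, and at most about 3% at SD 5.66. The false-positive rate from a pure period shift of 1 to 4 runs from 16% to 96% with 16 patients at SD 4, and from 10% to 75% at SD 5.66. This must be corrected before analysis.

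**What to change.** In the synopsis, section 4.1 and section 9.1, define the primary contrast by activity: (MRI after horticulture − MRI #1) minus (MRI after handiwork − MRI #1). That is MRI #2 − MRI #3 in the horticulture-first sequence and MRI #3 − MRI #2 in the handiwork-first sequence. State in section 13 that the two activities form the pair.

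Include period in the analysis, because the contrast by activity still carries π(nA − nB)/n when completers are unequal: a shift of 4 at 10:6 leaves 4 × 4/16 = 1.0. The simplest form compares MRI #2 − MRI #3 between the two sequences; half the difference in sequence means estimates τ.

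Give the biostatistician a masked A/B sequence code. The two-sided test can be run on it, and the direction read once the code is opened.

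The cost is a wording change in three places, a sentence in section 13 and one masked variable in the data extract. No new data, visits or patients are needed, and this change does not alter N.
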